### 7. Statistics and sample size justification

Sample size considerations focus on the primary hypothesis posited in the Specific Aims section. The major research goal is to determine the efficacy of having patients use the asthma module of the interactive website, for a period of 12 months, for improving asthma control. The primary outcome will be asthma control, based on the Asthma Control Test (ACT), a valid and reliable 5-question self-report measure of asthma control. 98-100. We chose to power the study based on asthma control, as it is a powerful predictor of emergency department visits, activity limitations and missing days of work due to asthma 6,100,130, and it is a central goal in both Healthy People 2010 as well as in the 2007 NAEPP Guidelines 26,131. We chose not to power the study on improving the use of controller medications, such as inhaled corticosteroid use, as the rates of use of these medications has increased greatly over the past decade, which would lead to a ceiling effect 7. Despite the broad use of these controller medications, however, asthma control rates are still in the 50% range, so we will not suffer from such a ceiling effect 5. Our estimated baseline rate of 55% is based on two studies of asthma control in similar groups of insured patients that both showed asthma control rates in the 50% range 5,6. For example, Schatz and colleagues observed that 48.4% of 570 insured adults with asthma had an Asthma Control Test (ACT) score of less than 20, the same measure of asthma control that we are using in the current study 5. Vollmer and colleagues reported that 48% of 5,181 insured adults with asthma reported good asthma control, using a slightly different measure of asthma control, the Asthma Quality of Life Questionnaire 6. We expect a slightly higher baseline control rate, as patients who volunteer for clinical trials tend to be healthier than those who do not 132. This expected effect size is based on a meta-analysis by Stone and colleagues that examined the efficacy of reminders, given to patients, on rates of adult immunization and cancer screening services 16. Patient reminders, similar to what we plan to use in the current study, significantly increased immunizations (odds ratio, OR=2.5), mammography utilization (OR=2.3), cervical cytology screening (OR=1.7) and colon cancer screening (OR=2.8). These effect sizes are consistent with reviews by other investigators 23,50,133. In the current study, we will be powered to detect an effect size that translates to a relative risk of 1.3 (0.70 /0.55) and odds ratio of 1.9. We chose this conservative effect size to address the fact that we are not examining a process of care but an outcome of care. While we expect the intervention to lead to increases in the number of controller medications used, additional medications do not always help patients. Also, we need to be sensitive to the possible differences in efficacy between interventions to increase adult preventive services (e.g., pap testing) and studies such as ours that seek to change chronic disease management practices. We considered powering on a numerical change in the Asthma Control Test (ACT), our main outcome measure, but chose not to do this as there is less consensus about what represents a meaningful change in the ACT than there is about what represents appropriate asthma control 5,98. We will, however, analyze changes in the ACT as a continuous variable, in our secondary analyses. Formulas based on the chi-square test were used to derive sample size calculations from the following assumptions. We assume a type I error rate (alpha) of 5% (0.05), 80% (0.80) power, and a two-tailed test, which allows us to detect significant differences in either direction. We expect a 12-month retention rate of 80%, although we believe that our procedures will substantially minimize the likelihood of attrition. We considered randomizing providers but felt that, given the number of providers in the two geographical areas, it was very unlikely that a physician would have more than one subject enrolled in the study. We will, however, track the name of the asthma care provider, so that we can include this variable in a sensitivity analysis, to be certain that adding this variable does not change the conclusions of the data analyses. In order to achieve 80% power to detect a difference of 70% vs. 55% between intervention and control group, we will need to randomize 408 patients into the two conditions at baseline. This assumes that no more than 20% are lost to follow-up at 12 months, leaving no fewer than 326 subjects available for analysis at the end of the study. We do concede, however, that smaller differences in asthma control may be clinically important, particularly on a population level. To power the study on a 10% difference in asthma control, however, we would have needed to recruit 940 subjects, which we felt would unnecessarily increase the cost and complexity of the study.

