
Preliminary data analysis plan: All analyses will be conducted using SAS Version 9. Initially, descriptive statistics such as the minimum, maximum, range, median, quartiles, mean, and standard deviation for each continuous variable and frequencies and percentages for each categorical variable will be used to summarize all variables as well as detect outliers, data entry mistakes, and missing values. These descriptives will be used to “clean” the data prior to analysis. Exploratory graphical techniques will be used to further examine these data. The normality of the distribution of mediators of interest, both in their original and transformed state (if necessary), will be examined with a normal probability plot when applicable. Longitudinal plots will be used to identify trends over time that are both population- and individually-based.

Differential dropout and attrition: Initially, the two randomized groups will be compared on important demographic and other baseline variables to ensure successful randomization. If it is determined that the groups, by chance, are significantly different on some measures, we will include those theoretically meaningful confounders as covariates in subsequent analyses. T-tests, ANOVA, and/or chi-square tests of independence comparing those who complete the study with those lost to follow-up will be performed on baseline demographic variables, asthma control, asthma-related quality of life, and baseline use of controller medications to identify potential differential dropout. These comparisons ensure equality of intervention and comparison groups after accounting for study attrition. For the primary outcome, we will apply intention to treat (ITT) principles with all available data included in the first set of analyses 134. Second, subjects lost to follow-up will be conservatively assumed to have not changed their level of asthma control between baseline and 12 months. Similar findings between both approaches would increase confidence in the results overall.

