Analysis of main outcome: Data analysis will focus on the primary hypotheses that significantly more subjects in the IC will have their asthma controlled, an Asthma Control Test (ACT) score of ≥ 20, than subjects in the CC. This dichotomized version of the ACT at 12 months is the primary outcome. We considered powering on a numerical change in the Asthma Control Test (ACT), our main outcome measure, but chose not to do this as there is less consensus about what represents a meaningful change in the ACT than there is about what represents appropriate asthma control 5,98. Logistic regression will be used to analyze asthma control at 12 months. Logistic regression allows for inclusion of the two dichotomous strata. Also, it is possible that the groups may have differences at baseline in potential confounders (e.g. socio-economic status, asthma symptoms) that may contribute to group differences in the 12 month event rate between the two conditions. Logistic regression permits inclusion of these potential confounders as covariates. Additionally, as the ACT is measured every 3 months, the logistic regression model can be extended using the generalized estimating equations (GEE) approach of Zeger and Liang (1986) with a logit link so that the repeated measures on each subject can be included in the analyses 137. Thus, asthma control can be examined at any of the preceding time points as well. Tests of the primary hypotheses about intervention effects will be formulated directly in terms of the main effect of intervention. We will also assign a create variables for physicians’ practices, so that physicians who practice together will be given the same variable number. In our analyses we first perform intent-to-treat (ITT) analyses and then will perform analysis including physician- and practice-level variables, while accounting for clustering.

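### A baseline significance test decides which covariates enter the primary analysis, so baseline ACT is not committed to the model and precision is forgone

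*Protocol*

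**What the plan says.** All of this is in the protocol, mostly in Section 7 (Statistics and sample size justification).

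- **Differential dropout and attrition.** The arms are compared at baseline to check the randomisation, and then: "If it is determined that the groups, by chance, are significantly different on some measures, we will include those theoretically meaningful confounders as covariates". A covariate must therefore show a significant difference and also have a theoretical rationale.
- **Analysis of main outcome.** The primary analysis is logistic regression of control (ACT of 20 or more) at 12 months. The text notes that the arms may differ at baseline, with socio-economic status and asthma symptoms as examples, and adds: "Logistic regression permits inclusion of these potential confounders as covariates". It also says: "Logistic regression allows for inclusion of the two dichotomous strata". The protocol never says what these strata are.
- **Sample size.** "We assume a type I error rate (alpha) of 5% (0.05), 80% (0.80) power, and a two-tailed test"; "In order to achieve 80% power to detect a difference of 70% vs. 55% between intervention and control group". The formula is for a chi-square test without covariates.
- **Expected control rate.** "Our estimated baseline rate of 55% is based on two studies of asthma control in similar groups of insured patients".

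The eligibility criteria set no ACT limit. The schedule in Section 5 collects ACT from every participant at baseline. Section 6 describes ACT as related to future asthma control.

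**The concern.** In a randomised trial, a baseline significance test can only detect chance, as the quoted sentence itself concedes. It is a poor guide to adjustment. A non-significant imbalance in a strong predictor still moves the estimate, and the benefit of adjusting for such a predictor does not depend on any imbalance.

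Baseline ACT is the obvious candidate here. It is the outcome measure itself, taken at entry, in a population of whom about 55% are expected to meet the primary endpoint already. Yet no sentence commits it to the primary model. Whether it enters depends on a test that will usually be non-significant, or on a permissive sentence with no criterion. At stake are a primary estimate and p-value whose model is settled after looking at the data, and precision that is available from data already being collected.

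**Working it through.** **Step 1. Reproduce the plan's figures.** Inputs from Section 7: 55% v 70%, two-sided alpha 0.05, power 80%, 20% loss. Equal allocation is assumed, since no ratio is stated. With pooled variance under the null and no continuity correction:

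n per arm = [1.96 × √(2 × 0.625 × 0.375) + 0.842 × √(0.55 × 0.45 + 0.70 × 0.30)]² / 0.15²

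= (1.342 + 0.569)² / 0.0225 ≈ 162.3, rounded up to 163.

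Total analysed = 326, and 326 / 0.80 = 407.5, rounded up to 408. Both match the protocol. Power at 163 per arm is 80.2%. The protocol's 940 for a 10-point difference also reproduces: 376 per arm, 752 / 0.80 = 940.

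**Step 2. How often the rule would pick up baseline ACT.** With randomised arms, a two-sided 5% test of baseline ACT is significant in 5% of trials by construction. The simulation below gave 4.6% to 5.6%.

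**Step 3. Power with and without adjustment.** There were 4,000 simulated trials per scenario with 163 per arm. Baseline and 12-month ACT were modelled as latent bivariate normal, with 55% controlled at entry and 55% v 70% controlled at 12 months. The correlation is an assumption. The treatment effect was tested by a logistic Wald test. The protocol's rule was represented as adjusting for continuous baseline ACT only when its baseline t-test was significant.

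| Assumed correlation | Unadjusted | Protocol's rule | Always adjust, ACT ≥ 20 v < 20 | Always adjust, continuous ACT | Gain, continuous v rule (points) |
|---|---|---|---|---|---|
| 0.3 | 79.1% | 79.2% | 80.4% | 81.2% | 2.0 |
| 0.4 | 80.7% | 81.2% | 83.2% | 84.8% | 3.6 |
| 0.5 | 80.3% | 81.0% | 84.8% | 86.6% | 5.6 |
| 0.6 | 80.7% | 81.4% | 86.3% | 89.1% | 7.7 |
| 0.7 | 79.8% | 81.3% | 90.0% | 93.0% | 11.7 |

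The Monte Carlo standard error near 80% is √(0.8 × 0.2 / 4000) = 0.6 points. A separate simulation gave 78% to 81% under the rule, and 81%, 82%, 87%, 90% and 92% with continuous ACT at the same five correlations.

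**Step 4. Type I error.** With 55% in both arms, the rule rejected in 4.0% to 5.2% of trials over these correlations.

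**Step 5. Effect on the odds ratio.** The planning odds ratio is (0.70/0.30) / (0.55/0.45) = 1.91. In the same latent model, the odds ratio conditional on continuous baseline ACT is 2.04, 2.16, 2.32 and 2.62 at correlations of 0.4, 0.5, 0.6 and 0.7.

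**The case against.** The strongest reply is that nothing promised is lost. The trial was sized for an unadjusted chi-square test. It delivers the stated 80% under the protocol's rule, and the test is valid. That stands: a reader might infer that 408 is too few or that the false-positive rate is inflated, and Steps 1 and 4 support neither.

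Second, the rule has a filter. Only covariates with a theoretical rationale qualify, so a chance difference in an irrelevant variable need not change the model. This also stands. A reader might be tempted to multiply out many baseline tests into a high probability of a changed model. The protocol gives no count of tests, the asthma measures are unlikely to be independent, and such a figure would ignore the filter.

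Third, the text does not exclude baseline ACT. The permissive sentence mentions asthma symptoms and sets no threshold, and one of the strata might be baseline control. That is possible, but nothing says so. A reader might equally infer that randomisation is unstratified. Sections 3 and 5 are silent on strata and refer only to an algorithm in the management module, so the supportable statement is that the strata are undefined.

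Fourth, the size of the gain is assumed, and at a correlation of 0.3 it is small. This stands and is carried into the verdict.

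Finally, covariate lists are often left to a statistical analysis plan, which is not shown here. But the protocol does not leave the matter open: it states a selection rule, and that rule is the problem.

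**Conclusion.** The point holds as one of efficiency and pre-specification. The protocol lets a baseline significance test choose covariates and does not commit baseline ACT to the primary model. The cost is a data-dependent primary analysis and forgone power of about 2 to 3 points at a correlation of 0.3, about 6 at 0.5 and about 12 at 0.7. These figures rest on equal allocation, 326 analysed, a latent-normal model and an assumed correlation, for which the protocol gives no value. That baseline ACT predicts 12-month control well is a reasonable expectation but not a documented fact. The sample size and the validity of the test are not in question. The undefined strata are a separate, smaller gap in the same paragraph. No additional mandatory interaction test follows from this point, since Section 7 already plans interaction terms for moderators.

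**What to change.** 1. State that the primary 12-month logistic model contains arm and continuous baseline ACT score, plus any strata actually used in randomisation, whatever imbalance is observed.
2. Delete the significance-test trigger and report baseline comparisons descriptively.
3. Name the two strata, or delete the sentence that mentions them.
4. Report a standardised risk difference next to the odds ratio, so that the result can be read against the planned 70% v 55%.

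No new data are needed and 408 need not change. The one real cost is interpretive. The adjusted odds ratio is conditional and will exceed the planning value of 1.9, at about 2.0 to 2.6 over correlations of 0.3 to 0.7. The text should therefore say which effect measure is primary.

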Missing data: For exploratory analyses, if the combined rate of missingness on predictor variables is less than 5%, the missing data will not be replaced. In the event of unanticipated higher levels of missing data, we need to examine the nature of the missing values. If it is believed that variations in attrition can be explained by observed variables (e.g. if those who are observed to have poorer asthma control at baseline are more likely to drop out), this corresponds to the missing at random (MAR) assumption and the models as we have specified them will give valid inferences because they are likelihood-based 135, and no special adjustments are necessary. If instead we believe that some of the variability in attrition might further be explained by variables not observed, then we will employ multiple imputation 136 (i.e., using PROC MI in SAS) which have been shown to yield estimates that are comparable to those that would be obtained if the data were all present. Because such imputations are necessarily based on assumptions that cannot be verified, we will carry out sensitivity analyses to investigate violations of these assumptions.

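### The attrition check has no arm term, so it cannot support the protocol's claim that the groups are equal after dropout

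*Protocol*

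**What the plan says.** The paragraph on differential dropout and attrition in Protocol III.7 describes two baseline comparisons.

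- **Before attrition.** It states that "the two randomized groups will be compared on important demographic and other baseline variables to ensure successful randomization". If the arms differ significantly by chance, the theoretically meaningful confounders become covariates.
- **After attrition.** T-tests, ANOVA and/or chi-square tests "comparing those who complete the study with those lost to follow-up will be performed on baseline demographic variables", and also on asthma control, quality of life "and baseline use of controller medications to identify potential differential dropout".

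The next sentence draws the conclusion: "These comparisons ensure equality of intervention and comparison groups after accounting for study attrition".

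The same paragraph plans two primary analyses: one on all available data, and one in which lost subjects keep their baseline control status. The paragraph on the main outcome says that logistic regression allows two strata, which it does not name, and permits covariates. It does not commit to baseline ACT as a covariate.

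**The concern.** The question after attrition is whether the subjects still observed in one arm are comparable with those still observed in the other. The planned comparison answers a different question: whether those who left differ from those who stayed. If uncontrolled patients leave one arm and controlled patients leave the other, the two patterns offset each other and the test sees nothing. If both arms lose the same kind of patient, the test is significant although the arms remain balanced.

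With 20% loss allowed for and an available-data analysis first in line, loss that differs by arm and is related to prognosis would bias the treatment comparison. The covariate rule does not catch it, because that rule looks at the arms as randomized.

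**Working it through.** **Inputs from Protocol III.7.** Two-sided alpha 0.05 and 80% power ("We assume a type I error rate (alpha) of 5% (0.05), 80% (0.80) power, and a two-tailed test"); 70% v 55% controlled; 408 randomized; 20% loss; 326 analysable; 55% estimated baseline control.

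**Assumptions.** 1:1 allocation, so 204 per arm. All retention rates by arm are assumed, because the protocol gives none. Tests are chi-square on expected counts without continuity correction.

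**The plan's own figure.** The mean proportion is 0.625. Per arm, n = [1.960·√(2·0.625·0.375) + 0.842·√(0.55·0.45 + 0.70·0.30)]² / 0.15² = (1.342 + 0.569)² / 0.0225 ≈ 162.3, so 163. Two arms give 326, and 326/0.8 = 407.5, so 408. The sample size reproduces and is not in dispute.

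**Opposite selection.** IC retains 90% of controlled and 70% of uncontrolled subjects; CC retains 70% and 90%.

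- IC retained: 0.55·0.9 + 0.45·0.7 = 0.495 + 0.315 = 0.81, about 39 lost.
- CC retained: 0.55·0.7 + 0.45·0.9 = 0.385 + 0.405 = 0.79, about 43 lost.
- The check as written: completers are (0.495 + 0.385)/(0.81 + 0.79) = 55.0% controlled at baseline. The lost are (0.055 + 0.165)/(0.19 + 0.21) = 55.0%. p = 1.00.
- Between arms among completers: 0.495/0.81 = 61.1% v 0.385/0.79 = 48.7%, p = 0.025.

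**Effect on the outcome with no true treatment effect.** Assume that 80% of subjects controlled at baseline are controlled at 12 months. To keep 55% overall, the rate in the uncontrolled must be (0.55 − 0.55·0.80)/0.45 = 24.4%.

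- Available data: IC 0.611·0.80 + 0.389·0.244 = 58.4%; CC 0.487·0.80 + 0.513·0.244 = 51.5%. Difference +6.9 points.
- No-change analysis: IC 0.495·0.80 + 0.315·0.244 + 0.055 = 52.8%; CC 0.385·0.80 + 0.405·0.244 + 0.165 = 57.2%. Difference −4.4 points.

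**Other assumed patterns.** Retention is shown as controlled/uncontrolled.

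| IC | CC | Check as written | Arms after attrition |
|---|---|---|---|
| 85/75 | 75/85 | p = 1.00 | Completers 6.2 points apart at baseline, p = 0.26; available data +3.4, no-change −2.2 |
| 90/70 | 90/70 | p < 0.001 | Completers identical, 61.1% each |
| 70/70 | 90/90 | p = 1.00 | Loss 30% v 10%, p = 4×10⁻⁷ by a direct test; baseline control unaffected |
| 90/70 | 80/80 | p = 0.011 (58.1% v 42.3%) | Completers 61.1% v 55.0% |
| 90/70 | 75/85 | p = 0.21 | Partly offsetting selection |

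The first row shows why the verb *ensure* would be wrong even for a check by arm: a 6.2-point gap is not significant. The second row is a false alarm about balance between arms, and the third a false reassurance about loss rates. In the fourth row the check does respond, but it does not show which arm is responsible.

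**The case against.** **Pooling is inferred.** The text does not say that the arms are combined, and an ANOVA could carry arm by completion. That is fair, but no such term is stated, and the conclusion about the arms is drawn from the comparison that is stated. An attrition table can be left to an SAP. A sentence claiming a result that the named comparison cannot deliver is an error in the protocol itself.

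**The check is not blind.** A reader might infer that it can never detect differential dropout. The documents do not support that: with selection in IC only (90/70 v 80/80) it gives p = 0.011. It fails fully when patterns cancel or when loss rates differ without relation to baseline, and it loses sensitivity when patterns partly cancel. Exact mirror-image selection is an illustrative extreme that no figure in the protocol suggests.

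**The no-change analysis would expose the problem.** This stands in part. In the example the two planned analyses have opposite signs, and the protocol ties confidence to their agreement. The discordance would be noticed, but neither result is the true zero, and the check would not explain why they differ.

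**Adjustment is available.** In the example, conditioning on baseline control removes the bias, and the main-outcome paragraph permits covariates and mentions asthma symptoms as a possible confounder. If one of the unnamed strata were baseline control, bias from that variable would shrink. Permission is not commitment, however, and the stated trigger looks only at the randomized groups.

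**The missing-data paragraph.** A reader might also infer that a null check leads to the clause "no special adjustments are necessary". The text does not say so. That paragraph opens with exploratory analyses and missing predictors, does not refer to these tests, and ties the clause to a belief that observed variables explain attrition. The point here does not rest on it.

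**Conclusion.** The point holds in a limited form. The check as written identifies overall selective loss on the listed variables. It does not identify loss that differs between arms, and it cannot ensure that the arms are equal after attrition. The claim to that effect is wrong whatever the retention pattern turns out to be.

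The possible size rests on assumption. Under the two mirror-image patterns above, the available-data analysis shows a spurious 3.4 to 6.9 points against a 15-point target while the check is null. These figures assume 1:1 allocation, 55% baseline control, 12-month control of 80% and 24.4% by baseline status, no treatment effect, and no adjustment for baseline control. They illustrate what the check can miss and do not predict bias in this trial. The sample size is unaffected, and the protocol does not make the primary test depend on the check. The correction should still be made, because a falsely reassuring statement sits beside a covariate rule that would not respond to imbalance created by attrition.

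**What to change.** 1. Report loss to follow-up, with reasons where known, by arm.
2. Compare baseline ACT and key covariates between arms among completers, or model completion on arm, baseline ACT and their interaction. Read the size of the differences as well as the p-values.
3. Prespecify baseline ACT as a covariate in the primary 12-month logistic model, whatever the baseline significance tests show.
4. Reword the concluding sentence so that the comparisons assess balance between the arms after attrition and are not said to ensure it.

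The cost is one table or model, one covariate and one sentence. Baseline ACT is already in the schedule of measures, and neither the sample size nor data collection changes.

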### 6. Primary and secondary outcome measures

**Primary Outcome measures:** Asthma control, health care utilization, pulmonary function and asthma-relate quality of life. The main aim of the intervention is to improve asthma control and improve quality of care for asthma, in keeping with the 2007 NAEPP Guidelines 29. The NAEPP guidelines state that the goals include “minimal or no chronic symptoms day or night” and “no limitations on activities” 29. We hypothesize that each of these measures will be improved in the IC, compared to the CC.

Asthma Control: We will measure asthma control using the Asthma Control Test (ACT), at baseline, 6 months, and 12 months. The ACT asks patients about several aspects of their asthma control over the past 4 weeks: a) whether their asthma interfered with their activities, b) how often they had shortness of breath from asthma, c) how often they used their rescue inhaler, d) how often they had asthma symptoms at night and e) an overall impression of their asthma control. The ACT has a test-retest reliability of 0.84 and compares closely with a specialist’s rating of asthma control, the need for change in patient’s therapy and percent predicted FEV1, future asthma control and future emergency department visits 98-100. The ACT is also sensitive to changes in asthma treatment 99. The overall agreement between ACT and the specialist’s rating ranged from 71% to 78% depending on the cut points used, and the area under the receiver operating characteristic curve was 0.77 98. An ACT score of ≥ 20 will be used as a cutoff for determining “controlled” v. “uncontrolled” asthma, as this cutoff demonstrated the highest area under the ROC curve. The use of the ACT, as well as the cutoff of 20 for determining control are supported in the 2007 NAEPP Guidelines on page 345 26. We hypothesize that, at 12 months, 70% of subjects in the IC condition will have an ACT of ≥ 20 versus only 55% in the CC condition.

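### Carrying baseline control status forward for lost subjects is not conservative by construction, and its agreement with the available-data analysis cannot rule out worsening after baseline among intervention dropouts

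*Protocol*

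**What the plan says.** Protocol section III.7, under *Differential dropout and attrition*, sets two analyses of the primary outcome. The first follows intention-to-treat principles "with all available data included in the first set of analyses". In the second, "subjects lost to follow-up will be conservatively assumed to have not changed their level of asthma control between baseline and 12 months". The protocol then says how to read the pair: "Similar findings between both approaches would increase confidence in the results overall".

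Other provisions bear on dropout:
- The same paragraph plans tests "comparing those who complete the study with those lost to follow-up will be performed on baseline demographic variables", and on baseline asthma control, quality of life and controller use.
- The *Missing data* paragraph begins "For exploratory analyses, if the combined rate of missingness on predictor variables is less than 5"%. It goes on to attrition: if unobserved variables may explain some of it, "then we will employ multiple imputation", and because such imputations cannot be verified, "we will carry out sensitivity analyses to investigate violations of these assumptions".
- Section III.6 gives the measurement times: "We will measure asthma control using the Asthma Control Test (ACT), at baseline, 6 months, and 12 months".
- *Analysis of main outcome* specifies logistic regression at 12 months and allows an extension by GEE that uses the repeated ACT values.

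**The concern.** The primary outcome is a state at 12 months, not an improvement from baseline. Section III.7 expects about 55% of subjects to be controlled at entry. If lost subjects resemble the rest at baseline, the rule scores about 55% of them as 12-month successes, including any who lost control and then stopped taking part. Whether this helps or hurts the asthma-module arm (IC) relative to the preventive-module arm (CC) depends on what happened to the dropouts after baseline, which the rule assumes away.

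For someone lost between months 6 and 12, the rule also uses the older baseline value even when the 6-month ACT already shows a change.

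Up to 20% of the primary outcome may be missing, about 82 of 408 subjects. If intervention dropouts worsened, both planned analyses can be too favourable together, and the plan would read their agreement as support.

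**Working it through.** **The plan's own figure.** Inputs from section III.7: 70% v 55%, two-sided alpha 0.05, 80% power, 20% loss. Allocation of 1:1 is assumed; it reproduces the stated total. With mean rate 0.625:

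n per arm = [1.96 × √(2 × 0.625 × 0.375) + 0.842 × √(0.70 × 0.30 + 0.55 × 0.45)]² / 0.15² = 162.3, so 163.

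That is 326 in total, and 326 / 0.8 = 407.5, so 408. The sample size is reproduced and is not in dispute.

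**Bias of the rule.** For each arm let d be the proportion lost, b the baseline control rate among those lost, and t their true 12-month rate. The carried-forward arm rate is (1 − d) × completer rate + d × b. The true arm rate has t in place of b. So:

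bias of the IC − CC difference = d_IC × (b_IC − t_IC) − d_CC × (b_CC − t_CC).

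The sign depends on the two t values, which are unobserved. Nothing in the rule makes it zero or negative.

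**Planning figures.** 204 per arm, 163 complete and 41 lost, completers 70% v 55%, b = 55% in both arms, CC dropouts at 55%.
- Available data: 15.0 points, z = 2.80, p = 0.005.
- Carried forward: IC (0.70 × 163 + 0.55 × 41) / 204 = 67.0%; CC 55%. Difference 12.0 points, z = 2.48, p = 0.013.

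These two results are the same in every row below. Only the assumed true control rate among IC dropouts changes; the protocol gives no such rate. The p-value is from a pooled z-test on the complete cohort.

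| IC dropouts controlled at 12 months (assumed) | True difference | p, complete cohort | Bias of carried-forward result |
|---|---|---|---|
| 70% | 15.0 points | 0.002 | −3 |
| 55% | 12.0 | 0.013 | 0 |
| 45% | 10.0 | 0.040 | +2 |
| 35% | 8.0 | 0.10 | +4 |
| 25% | 6.0 | 0.22 | +6 |
| 15% | 4.0 | 0.42 | +8 |

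In this illustration the complete-cohort result loses significance somewhere between 45% and 35%, while both planned analyses stay significant.

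**The opposite direction.** If CC dropouts fell to 35% and IC dropouts stayed at 55%, the true difference is (0.8 × 0.70 + 0.2 × 0.55) − (0.8 × 0.55 + 0.2 × 0.35) = 0.67 − 0.51 = 16 points. The rule gives 12, so it understates the effect by 4.

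**Unequal loss with no effect.** If both arms improve from 55% to 65% and loss is 10% in IC and 30% in CC (assumed), the rule gives 0.9 × 0.65 + 0.1 × 0.55 = 64% against 0.7 × 0.65 + 0.3 × 0.55 = 62%. That is a spurious +2 points. Swapping the loss rates gives −2.

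**The case against.** Much can be said for the plan.

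- A reader might infer that this rule is the only check on dropout. It is not. The plan also compares completers with lost subjects at baseline and promises multiple imputation and sensitivity analyses. These do not cure the rule, however. A baseline comparison cannot show worsening after baseline. The *Missing data* paragraph opens on exploratory analyses and predictor variables, although it then turns to attrition. It calls the models likelihood-based, which a GEE is not, and assigns multiple imputation to missingness driven by unobserved variables, where standard imputation ordinarily assumes missing at random. That its sensitivity analyses are unnamed is not held against it, since a SAP may name them.
- A reader might infer that the plan ignores the 6-month ACT. Only this rule does. The GEE extension could use it, but is optional.
- Under the planning figures the rule moves the estimate towards no effect. With equal loss and equal baseline control among the lost, the carried-forward difference is (1 − d) times the completer difference, here 0.8 × 15 = 12. That is a fair sense of conservative, but it is attenuation relative to the first analysis, not protection against overstating the true effect.
- If dropouts were already worse at baseline, the rule removes some or all of the bias, and the two analyses diverge as they should. Take no true effect, with IC completers at 61.25% and CC at 55%. If lost IC subjects were 40% controlled at baseline, the rule gives 0.8 × 61.25 + 0.2 × 40 = 57%; at 30% it gives 55%. Agreement is therefore not built in. The blind spot is change after baseline.
- Nothing in the protocol suggests that only IC dropouts would worsen. If dropouts in both arms fall equally, with equal loss, the bias is zero.

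**Conclusion.** The point holds in a limited form. The rule is stated concretely and labelled conservative, but the label is not justified because the bias can go either way. With 20% loss and 55% baseline control, it understates the effect by 3 points if IC dropouts reached 70%, is exact at 55%, and overstates by 2 to 8 points if they fell to between 45% and 15%, with CC dropouts at 55% throughout. These dropout rates are assumptions, and the tests are unadjusted.

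The first analysis, taken as the specified 12-month logistic regression, and the carried-forward analysis both leave the dropouts' post-baseline status out. Their agreement can therefore be false reassurance about worsening after baseline. The documents do not support saying that it always is, or that the rule systematically favours the intervention. Nor does the protocol make agreement a formal test of robustness; it says only that agreement would add confidence.

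**What to change.** In section III.7, *Differential dropout and attrition*:

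1. Delete *conservatively*.
2. For the primary outcome, multiply impute 12-month control within each arm from baseline and 6-month ACT.
3. Then vary the control rate of missing subjects separately by arm, including lowering it in IC while CC is held at its imputed rate. Report the point at which the conclusion changes, and base the statement on robustness on that.
4. Keep baseline carried forward only as a descriptive supplementary analysis.

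The cost is wording and a few more analysis runs on data already collected, with no change to sample size or conduct. The downside is that the robustness statement may turn out less favourable.
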